#### Objective 1 outcome measures

Beginning 4 months after randomization, each caregiver-child dyad will be followed for a period of 12–48 months to document all CPS investigations of suspected CM. The length of the follow-up interval will depend on the dyad’s time of enrollment in the study. The primary outcome is a binary indicator of whether the caregiver-child dyad experienced at least one CPS investigation during follow-up. Investigations (unsubstantiated and substantiated) of CM rather than substantiations will be used because children with unsubstantiated reports and those with substantiated reports face similar rates of negative outcomes such as CM re-reports, negative impact on school achievement, and mortality [55–59].

#### Objective 2 outcome measures

CM risk, harsh, neglectful, and dysfunctional parenting, child behavior problems, caregiver stress, and caregiver-child interactions (*n*=120) will be measured prior to randomization and 6-8 months later. The anticipated result is that the intervention will improve these scores to varying degrees. See Table 1 and Fig. 2 for data collection timeline.

**Table 1 Tab1:** Schedule of evaluations for quantitative objectives 1–3

Variables measured	Obj 1	Obj 2	Obj 3	Instrument	Occasions (months)		
					0	6–8	4–52
Demographics	Covariates	Covariates	Covariates	Self-report for caregiver and child	✓		
Spanish-speaking	Covariate	Covariate	Covariate	Self-report for caregiver	✓		
Caregiver depression	Moderator	Moderator		Patient Health Questionnaire-9 (PHQ-9)	✓		
Caregiver anxiety	Moderator	Moderator		General Anxiety Disorder-7 (GAD-7)	✓		
Caregiver ACEs	Moderator	Moderator		Adverse Child Experiences (ACE)	✓		
Child behavior problems		Dependent	Mediator	Eyberg Child Behavior Inventory (ECBI)	✓	✓	
Harsh parenting		Dependent	Mediator	Conflict Tactics Scales, Parent-Child version (CTS-PC)	✓	✓	
Dysfunctional parenting		Dependent	Mediator	Parenting Scale (PS)	✓	✓	
Caregiver-child interactions^b^		Dependent		Dyadic Parent-Child Interaction Coding System (DPICS)	✓	✓	
Caregiver stress		Dependent	Mediator	Parenting Stress Index-Short Form (PSI-SF)	✓	✓	
Maltreatment risk		Dependent	Dependent	Brief Child Abuse Potential Inventory (BCAP)	✓	✓	
Child maltreatment^**a**^	Dependent		Dependent	Child Protective Services (CPS) investigation			✓

^a^The length of follow-up data collection for CPS investigations will vary by participant depending on time of enrollment but will be up to 48 months (52 months after enrollment)

^b^Recorded for a subsample of 120 dyads

*CM risk will be measured by the Brief Child Abuse Potential Inventory (BCAP)*, a questionnaire that measures CM risk and includes a 34-item Child Physical Abuse scale [60]. The two internal validity scales can be used to create validity subtests: lie and random response [60]. BCAP is a brief version of the Child Abuse Potential Inventory and on cross-validation, BCAP risk scale scores demonstrated an internal consistency of 0.89 and substantial correlation with the Child Abuse Potential Inventory abuse risk score (r=0.96) [60, 61].

*Harsh and neglectful parenting will be measured by the Conflict Tactics Scales, Parent-Child version (CTS-PC)*, a 35-item scale focusing on the respondent’s behavior with their child including discipline methods. In this study, we will include the 18 items that constitute the nonviolent discipline, psychological aggression, and corporal punishment subscales [62–64]. We will not include the neglect, sexual abuse, physical assault, or physical maltreatment subscales of the CTS in order to minimize the potential legal risk to caregivers related to mandatory reporting laws. Reliability coefficients are moderate, with alpha coefficients of 0.70 for nonviolent discipline, 0.68 for psychological aggression, and 0.72 for corporal punishment [62–64]. The CTSPC has adequate discriminant and construct validity [62, 63]. Test-retest reliability has been established with a correlation of 0.8 at 5 months [62].

*Dysfunctional discipline will be measured by the Parenting Scale (PS)*, a 30-item self-report questionnaire designed to assess dysfunctional parenting discipline strategies including laxness (permissive inconsistent discipline, providing positive consequences for misbehavior), over-reactivity (harsh, emotional, authoritarian discipline characterized by irritability), and hostility (use of verbal or physical force). The PS has demonstrated adequate psychometric properties including internal consistency, test-retest reliability, and convergent validity with other validated measures, and is correlated with observational measures of inadequate parental discipline and child misbehavior [65–67].

*Child behavior problems will be measured by the Eyberg Child Behavior Inventory (ECBI)*, a 36-item parent survey used to assess the current frequency and severity of disruptive behaviors at home in children 2–16 years [68]. The test-retest reliability of the ECBI has been established with correlations near 0.75 for both subscales over a 10-month interval [69]. ECBI scores are highly correlated with observational measures of child negative affect, non-acceptance, and dominance [70]. The ECBI is also correlated with other measures of child behavior problems (has convergent validity) and conversely the ECBI has high discriminant validity. The ECBI is a sensitive indicator of intervention efficacy/effectiveness [71, 72].

*Caregiver stress will be measured by the Parenting Stress Index-Short Form (PSI-SF)*, a 36-item symptom inventory that can be used to identify caregiver-child dyads who are experiencing stress and at risk for dysfunctional parenting and behavior problems [73]. Psychometric evaluation of the PSI has demonstrated excellent internal consistency with a Cronbach’s alpha of 0.91 and excellent test-retest reliability with a Cronbach’s alpha of 0.84 for total stress [74].

*Caregiver-child interactions will be measured by the Dyadic Parent-Child Interaction Coding System (DPICS),* a coding system for specific structured caregiver-child interactions targeted by PriCARE [75]. DPICS includes codes for parent (commands, criticism, labeled praise) and child (noncompliance, compliance) behaviors. Inter-rater reliability, test-retest reliability, and convergent and discriminant validity are high [76, 77]. Caregivers and children are observed during two 5-min standard situations with instructions that produce opportunities to demonstrate differing levels of parental control: child-led play and clean-up. For a subsample of 120 enrolled dyads, these interactions will be video-recorded and coded by a team member trained to code DPICS and blinded to the study regimen.

#### Objective 3 outcome measures

We will investigate the roles of harsh/neglectful/dysfunctional parenting (CTS-PC and PS), parent stress (PSI-SF), and child behavior (ECBI) as potential mediators of the relationship between exposure to the PriCARE/*CARIÑO* intervention and outcomes of interest: occurrence of CPS investigations and CM risk scores (BCAP). The survey scales will be measured prior to randomization and 6-8 months later.

#### Objective 4 outcome measures

In addition to effectiveness outcomes, we will explore the relationship between implementation determinants (i.e., barriers and facilitators) and key implementation outcomes, including referral rates, enrollment rates, and attendance.

##### Implementation determinants

Semi-structured interviews, guided by the Theoretical Domains Framework (TDF) will be used to understand implementation determinants of PriCARE/*CARIÑO* across varied clinical settings [78–80]. The TDF is an ideal framework for our study because, in addition to being applied to explore barriers and facilitators to clinician implementation of evidence-based behaviors [81], it has also been extended to understanding patient behaviors [82], to identify mechanisms of change [83–85], and to identify and design strategies to address implementation barriers [86].

##### Referral rates

*Referral rates* will be measured at the clinic level and will be defined as the number of patients referred to PriCARE/*CARIÑO* divided by the number of eligible patient encounters during the study period. Referrals will be auto-captured through the Electronic Medical Record (EMR) and will be divided by the total number of eligible patient encounters. Eligible patient encounters will be defined as well visits for children 2 to 6 years old who have Medicaid, CHIP, or no insurance and whose caregivers speak English or Spanish and have not previously participated in PriCARE/*CARIÑO*.

##### Enrollment rates

*Enrollment rates* be measured at the clinic level and will be defined as the number of dyads who are referred and enroll in the study divided by the total number of eligible dyads referred to the study.

##### Attendance

*Attendance* will be recorded by research coordinators and will include the number of sessions (0–6) attended by each caregiver randomized to PriCARE/*CARIÑO*. Mean attendance will be calculated for each clinic.

#### Objective 5 outcome measures

This observational ancillary study will focus on longitudinal changes in the Eyberg Child Behavior Inventory (ECBI) Intensity Scale score (range 36–252). Summed across 36 items, lower scores are more favorable. The ECBI was the primary outcome measure in the three prior randomized clinical trials (historical data) and is a secondary outcome in this study (prospectively observed).

### Participant timeline {13}

The participant timeline is shown in Fig. 2.

### Sample size {14}

The study to be conducted in 10–15 clinics will enroll 1932 eligible caregiver-child dyads drawn from the target population of low-income children 2–6 years of age. We anticipate that about 15% of the caregivers will be Spanish speakers. We anticipate that about 200–300 of the 1932 enrolled dyads will experience CPS investigation during the study after 1:1 randomization stratified by clinical site and language. In designing the study and choosing the target sample size, considerations included (1) information from previous studies; (2) the availability of eligible dyads, clinics, and clinic personnel; (3) costs and time requirements; (4) anticipated frequencies of drop-out, missing data values, and nonadherence to protocol; (5) the statistical analysis strategies and methods specified for each of the five objectives; (6) anticipated levels of precision of estimators of key population parameters (estimands); and (7) anticipated levels of power of a hypothesis test procedure concerning the effectiveness of the intervention.

#### Objective 1 considerations

Considerations for Objective 1 were informed by the following published reports: during a 43-month study of 250 children in Baltimore (92% Medicaid), 19% had at least one CPS investigation [87]. In a state-wide prospective observational study in California, 21% of children with Medicaid at birth had at least one CPS investigation over 5 years [58]. In Cleveland, from birth to age 10, 31% of children were investigated by CPS [88]. An estimated 37% of all US children will have been investigated by CPS by the time they reach age 18 years [1]. These reports suggested that if our target population receives usual clinical care only and each child is followed for 12 to 48 months thereafter, then about 20% of the children would experience at least one CPS investigation during follow-up.

Assumptions: The statistical analyses will rely on generalized logistic regression models with *clinical site* treated as a categorical random effect, and with fixed effects representing *length of follow-up* (log_10_ months), *treatment regimen*, and *language* (Spanish-speaking). Additionally, variations on the model will be used to explore additional fixed effects; e.g., demographic characteristics, caregiver scores (*PHQ9, GAD7, ACEs*) at enrollment, and terms representing interactions among the fixed-effects.

To avoid model overfitting bias, we require at least 20 cases (20 dyads experiencing CPS investigation) per fixed-effect regression coefficient included in the model; e.g., if 200 cases occur, the models can support up to 10 coefficients in the regression equation. We anticipate that the chosen sample size is sufficient and appropriate for supporting objective 1.

For considerations of precision and power, simplifying assumptions and conjectures were made:the proportion (π_1_) experiencing CPS investigation is 20% in the target population when receiving only usual care, the proportion (π_2_) is 13% when the target population receives usual care plus the PriCARE/*CARIÑO* intervention, the follow-up interval is the same for all the small groups, and that intraclass correlation due to dyad clustering of dyads is small (*ρ* ≤ 0.15). In regard to precision, discussed in terms of the widths of 95% confidence intervals (CI): if the observed proportion of cases for the control regimen happens to be 20%, then the observed 95% CI for π_1_ would be {20.0% ± 4.0%}; if the observed proportion for the intervention regimen is 13%, then the observed 95% CI for π_2_ would be {13.0% ± 3.3%}; and the observed 95% CI for the difference (π_1_ − π_2_) would be {7.0% ± 4.5%}, approximately. In regard to power for the test of H_o_ “the treatment effect (π_1_ − π_2_) is exactly zero in the target population,” if (π_1_ − π_2_) = 7.0% then there is an 80% chance that a sample of dyads will be drawn from the target population such that a small *p*-value (< *α*=0.05) will be observed. If H_o_ is true then the power level is 5%.

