## Assignment of interventions: allocation

### Sequence generation {16a}

Enrolled dyads will be assigned by 1:1 stratified randomization to PriCARE/*CARIÑO* plus usual care or to usual care alone. The randomization schedule, stratified by *clinical site* and *language*, will be generated using permuted blocks of sizes 2 and 4 in an unpredictable order. This means that prior to the start of recruitment we will have created two separate allocation tables for each clinical site. Each allocation table will be sufficiently extensive to accommodate an unexpectedly large cohort. The allocation tables will be concealed from the study personnel during the study.

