##### Evaluation of effectiveness

For the primary analysis of the proportion of children with at least one CPS investigation during follow-up, we will use a logistic regression model with covariate adjustment for the length of follow-up (log_10_ months). To account for the clustering of dyads within clinical sites and within small groups of 8-10 for PriCARE sessions, the model will be fitted using generalized estimating equation (GEE) methods with robust standard error estimates. *Clinical site* will be treated as a random effect. To improve precision of the estimators of *regimen*-specific treatment effects, caregiver *language* (Spanish speaking) will be included as a covariate. This model assumes that the difference between regimens is not a function of *language*. The population parameters (estimands [90]) of interest are the regression coefficients, the regimen-and-language-specific proportions that would be expected during 12–48 months of follow-up, and the treatment effect (expected difference between proportions) along with its odds ratio. The point estimates and 95% CI estimates for these estimands will be presented graphically in a figure using a forest-plot format. The p-value for the treatment effect will be shown to four decimal places and will be interpreted as a continuous score [91–93]. The *S*-value = log_2_ (^1^/_*p* value_) representing the available amount of information (Shannon information) against the null hypothesis “the treatment effect is exactly zero” will also be shown in the figure.

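### The printed interval for the difference (±4.5 points) and the printed 80% power cannot both hold: ±4.5 implies about 86% power, and 80% needs about ±4.9

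*Protocol article*

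**What the plan says.** The trial "will enroll 1932 eligible caregiver-child dyads", and "Enrolled dyads will be assigned by 1:1 stratified randomization", which gives 966 per arm. Objective 1 considerations assumes that the proportion "experiencing CPS investigation is 20% in the target population when receiving only usual care" and that it is 13% with the intervention. It also assumes that the "intraclass correlation due to dyad clustering of dyads is small", with ρ at most 0.15.

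Four results follow in the same paragraph:

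- The control interval "would be {20.0% ± 4.0" points.
- The intervention interval is 13.0% ± 3.3 points.
- The interval for the difference "would be {7.0% ± 4.5%}, approximately".
- If the true difference is 7.0 points, "then there is an 80% chance that a sample of dyads will be drawn from the target population" that yields p < 0.05.

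The paragraph gives no cluster size or design effect, and does not say which cluster level or arm ρ refers to. It mentions only small groups. The objective 1 analysis (Evaluation of effectiveness) names two levels of clustering: clinical site, and dyads "within small groups of 8-10 for PriCARE sessions". Intervention description {11a} puts group size at about 4–10.

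**The concern.** The interval for the difference and the power statement concern the same estimator, the same 7.0-point difference and the same α. One standard error therefore fixes both, and the printed pair does not correspond to a single standard error.

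This paragraph is the quantitative justification printed for the primary endpoint. Depending on which figure is taken as correct, the design has about 75%, 80% or 86% power. A reader cannot tell what difference the trial can detect or exclude, or how much clustering was allowed for.

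**Working it through.** **Inputs.** n = 966 per arm (1932 at 1:1); 20% and 13%; two-sided α = 0.05, z = 1.96; ρ = 0.15, the stated upper bound. Group size m is 8–10 in the analysis section and 4–10 in the intervention description.

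**Step 1: interval against power.** This step needs no clustering input.

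- SE = 4.5/1.96 = 2.296 points.
- Power = Φ(7.0/2.296 − 1.96) = 86.2%.
- Rounding: ±4.45 gives 86.9% and ±4.55 gives 85.4%.
- Half-width needed for 80% power: 1.96 × 7.0/(1.96 + 0.842) = 4.90 points.
- Variants: a continuity correction gives 84%. Using t quantiles with 9 or 14 degrees of freedom raises the power to 87–88%. A two-sided α of 0.025 would give 79%, but the plan states 0.05.

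**Step 2: implied design effects.** The unclustered half-width is 1.96 × √(p(1−p)/n), and the design effect (DE) is (printed/unclustered)².

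| Printed figure | Unclustered | Implied DE | Range over rounding |
|---|---|---|---|
| Control ±4.0 | 2.52 | 2.51 | 2.45–2.58 |
| Intervention ±3.3 | 2.12 | 2.42 | 2.35–2.49 |
| Difference ±4.5 | 3.30 | 1.86 | 1.82–1.91 |
| 80% power | 441 per arm needed | 966/441 = 2.19 | – |

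The two single-arm figures share a DE of 2.45–2.49 within rounding, so there are three distinct values: about 2.47, 1.86 and 2.2.

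**Step 3: combining the single-arm intervals.**

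- Independent arms: √(4.0² + 3.3²) = 5.19 points. Power = Φ(7.0/(5.19/1.96) − 1.96) = 75%.
- Between-arm correlation needed to reach ±4.5: (4.0² + 3.3² − 4.5²)/(2 × 4.0 × 3.3) = 6.64/26.4 = 0.25 (0.21–0.29 over rounding). The SE is then still 2.296 points, so power is still 86%.

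**Step 4: reproducing the 80%.** Take DE = 1 + (m − 1)ρ with ρ = 0.15, applied to both arms.

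| m | DE | Control | Intervention | Difference | Power |
|---|---|---|---|---|---|
| 7 | 1.90 | ±3.5 | ±2.9 | ±4.5 | 85% |
| 8 | 2.05 | ±3.6 | ±3.0 | ±4.7 | 83% |
| 9 | 2.20 | ±3.7 | ±3.1 | ±4.9 | 80% |
| 10 | 2.35 | ±3.9 | ±3.3 | ±5.1 | 77% |

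The 80% reproduces at m = 9, the midpoint of 8–10. It also reproduces at m = 8 with a continuity correction (80.3%). The ±4.5 reproduces at m = 7, the midpoint of 4–10. These are possible origins only; the article does not give the derivation.

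**Step 5: group clustering in the intervention arm only, with no clinic effect.** At m = 9 the half-widths are ±2.5 for control, ±3.1 for intervention and √(2.52² + 2.12² × 2.2) = ±4.0 for the difference. Power is about 93% (93.5% at m = 8, 91.5% at m = 10).

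**The case against.** The paragraph presents its inputs as simplifications and conjectures, gives ρ as an upper bound and calls the interval for the difference approximate. The article is also a condensed version of the full protocol, where the design effect may be derived. This excuses the missing derivation. It does not excuse two printed results that need different standard errors: approximation does not stretch 4.5 to 4.9.

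A second defence is that the three intervals can coexist. Each clinic contains both arms, so shared clinic effects could correlate the arm estimates. A DE of 2.47 in both arms with a correlation of 0.25 gives ±3.96, ±3.33 and ±4.50. This stands, and it means the intervals do not by themselves contradict one another. The correlation is not stated, however, and it leaves power at 86%.

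A reader might also infer that group clustering was wrongly charged to usual-care dyads, who attend no groups, so that the control interval is too wide and the real power is about 93%. The match at m = 9 in both arms suggests this but does not show it. Clinical site is a named clustering level too, and a control DE of 2.47 needs a clinic intraclass correlation of only 0.015–0.023 with 64–97 control dyads per clinic (966 over 15 or 10 clinics).

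Nor is 93% safe as a replacement. Suppose, as an assumption, that clinic clustering alone gives a DE of 2.0 in each arm, on top of the group effect at m = 9. The variance inflation is then 2.0 for control and 3.2 for intervention. Power is about 75% if clinic effects are uncorrelated between arms, 82% at a correlation of 0.4 and 92% at 1.

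**Conclusion.** The point holds for the consistency of the printed figures. As stated, ±4.5 points means about 86% power and 80% power means about ±4.9 points, so at least one of the two is wrong. This rests only on a normal-approximation interval and test that share one standard error at two-sided α = 0.05, which is how the paragraph frames them.

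The wider mismatch among the design effects rests on 966 analysed dyads per arm. The 75% figure also assumes independent arms. The documents do not show which figure is wrong, that the control arm was charged for group clustering, or that the sample is too small.

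**What to change.** Rewrite the paragraph so that all three half-widths and the power come from one stated model. It should give:

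- the cluster level: clinic, PriCARE group or both;
- the cluster size, after reconciling 4–10 with 8–10;
- the intraclass correlation for each arm, with group clustering in the intervention arm only and any clinic clustering in both arms;
- any correlation between arms that is assumed through shared clinics, and the number of dyads analysed.

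Two coherent sets show the form, both at 966 per arm, m = 9 and ρ = 0.15. One DE of 2.2 in both arms gives ±3.7, ±3.1, ±4.9 and 80%. Group clustering in the intervention arm only, conditional on no clinic effect, gives ±2.5, ±3.1, ±4.0 and about 93%. The second set should be printed only with that condition attached.

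The cost is one recalculation and one rewritten paragraph. Enrolment, randomization and data collection do not change.

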#### Objective 2 considerations

We conjecture that the intervention improves proximal outcome scores: CM risk, child behavior problems, caregiver-child interactions (*n*=120), caregiver stress, harsh parenting by the caregiver, and dysfunctional parenting by the caregiver all measured prior to randomization and 6–8 months later. Based on prior studies we anticipate a 10% loss to follow-up at the 6-month interview.

#### Objective 3 considerations

The investigation of mediation effects will focus on model-building, estimation of effects, and qualitative analysis for purposes of hypothesis generation/refinement. We anticipate that the study design and target sample size will be adequate for these exploratory analyses.

